## Sample size calculation

The impact of total aortic arch repair compared to more limited aortic resection on the early and late outcomes will be one of the main topics of research from this registry. Therefore, in the light of the expected limited frequency of this surgical strategy, we performed a sample size analysis considering the extent of distal aortic resection. Despite the limitation of a pooled analysis which did not take in to account the cumulative incidences from competing risk analysis and the segment of repeat operation, Poon et al. [23] estimated a pooled hazard ratio on 0.73 (95%CI 0.56–1.18) of freedom from any late aortic reoperation for total arch replacement. Based on this hazard ratio, a sample size of 163 patients per study groups would be enough to reject the null hypothesis (alpha 0.05, power 0.80). Pan et al. [24] reported a freedom from distal reoperation after ascending aortic resection at 8 years of 95.3% which was not statistically different from that of hemiarch or total aortic arch repair (92.4%, *p* = 0.22). For the sample size calculation of a non-inferiority trial, we assumed a freedom rate from distal aortic reoperation of 95% and we considered that a difference in the reoperation rate as large as 10% in favor of a total aortic arch repair still allow the less extensive repair to be non-inferior (delta = 0.1, power 0.90, one-sided confidence 97.5%), the required sample size would be 100 patients per each group. We assume that about 5% of patients have undergone total arch repair in this collaborative registry and therefore a study population of 4000 patients would be enough to investigate the impact of total aortic arch repair in preventing late aortic reoperation in patients with acute TAAD. The participating hospitals are expected to provide a sample size of more than 6000 patients (i.e. at least a mean of > 20 procedures for acute TAAD each year), which would prevent a type II error.

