## Statistical analysis

Statistical analyses will be conducted using Stata v. 15.1 (StataCorp LLC, Texas, USA) and SPSS v. 27.0 (IBM Corporation, Armonk, NY, USA) statistical softwares. Continuous variables and outcomes will be reported as mean and standard deviation as well as median and interquartile range. Categorical variables and outcomes will be reported as counts and percentages. A *p* < 0.05 will be set for statistical significance. Differences between the study groups will be evaluated using the Fisher’s exact test, the Chi-square test, the linear-by-linear association test, the Mann-Whitney test and the Kruskall-Wallis test. The McNemar test and paired samples T-test will be used in the paired groups. Propensity score matching will be performed to balance treatment strategies for baseline differences. A propensity score will be estimated using a non-parsimonious multilevel mixed-effects logistic regression considering the cluster effect of the participating centers whose results may be affected by the referral pathway, surgical techniques and perioperative care. Multilevel mixed-effects logistic regression model will include all available baseline variables. The estimated propensity score will be employed for inverse propensity score weighting analysis and one-to-one propensity score matching analysis using a caliper width of 0.1 to 0.2 of the standard deviation of the estimated logit. Standardized differences < 0.10 will be considered an acceptable imbalance between the matched cohorts.

Survival analysis will be performed using the Kaplan-Meier method with the log-rank test and the Cox proportional hazards method. Competing risk analysis with the Gray’s test will be performed for late non-fatal adverse events because patient’s death might hinder the observation of these events. Regression models will include covariates with *p* < 0.05 or *p* < 0.2 in univariate analysis according to the number of covariates of interest. Risk estimates will reported as hazard ratios and subdistribution hazard ratios with their 95% confidence intervals.

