Logistic and linear regression analyses will be employed to identify independent risk factors for early adverse events with and without a stepwise approach. For the purpose of developing a risk scoring method from this registry, the study cohort will be randomly divided into two datasets, i.e. the derivation data set (75.0% of patients) and the validation data set (25.0% of patients). Univariate analysis will be performed on all candidate covariates of the derivation dataset to identify predictors of in-hospital mortality. Multiple logistic regression analysis will be then performed using the derivation dataset. A stepwise procedure with a bootstrap approach will be used, and 100 samples will be extracted with a size of 70% of the derivation dataset. A stepwise procedure will be applied to each sample (probability to stay = 0.05; probability to entry = 0.1). Variables selected in at least 50% of the stepwise procedures will be included in the regression model. Additional covariates were selected using a forward selection comparing the Akaike information criterion for the models with and without each covariate. The model with the lowest Akaike information criterion will be selected for each forward step, until the inclusion of a new covariate determined an increase in the Akaike information criterion value. The model will be tested in the validation data set for calibration, using the Hosmer–Lemeshow test, and for discrimination using the receiver-operating characteristic curve analysis. A comparison of the predictive ability of the new score with the current risk scoring methods for prediction of in-hospital mortality will be performed in the overall dataset as well as in the validation dataset using the DeLong test. The improvement of discrimination of the new score will be estimated by calculating the net reclassification index and the integrated discrimination improvement. Finally, to evaluate the adaptability of the new score for prediction of late mortality, Kaplan–Meier curves stratified by deciles of the new score will be plotted.

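### Covariates for the Cox and subdistribution-hazard models are chosen by univariate p-value, with two permitted cut-offs and no rule for choosing between them

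*Protocol article*

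**What the plan says.** In the Statistical analysis section, the paragraph on Kaplan-Meier, Cox and competing-risk methods sets the entry rule: "Regression models will include covariates with *p* < 0.05 or *p* < 0.2", followed by "in univariate analysis according to the number of covariates of interest". The next sentence makes these models the source of reported results: "Risk estimates will reported as hazard ratios and subdistribution hazard ratios with their 95% confidence intervals". Late mortality and aortic reoperation, which the Abstract lists among the primary outcomes, are the outcomes to which these methods apply.

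The preceding paragraph takes the opposite approach for the propensity score used to compare treatment strategies: "Multilevel mixed-effects logistic regression model will include all available baseline variables". That score accounts for clustering by centre, and it feeds both inverse weighting and one-to-one matching.

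Early outcomes have their own sentence: "Logistic and linear regression analyses will be employed to identify independent risk factors for early adverse events with and without a stepwise approach".

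**The concern.** There are two faults in the rule.

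- **Criterion.** Whether a covariate confounds a comparison depends on its relation to both the exposure and the outcome, given the other covariates. An unadjusted outcome p-value measures only one of these, and it depends heavily on the number of events. A variable strongly tied to the choice of repair, but only moderately tied to a rare outcome or masked by another factor, can fail the screen and still bias the adjusted estimate.
- **Cut-off.** Two thresholds are allowed, and no count of covariates or events decides between them. Two analysts following the text could fit different models to the same data and both be compliant.

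A confidence interval from the final model also treats the selected covariates as if they had been fixed in advance. At stake are the regression-adjusted hazard ratios for late mortality and reoperation, and the lists of independent risk factors drawn from the same models. The Background describes patient condition as limiting how extensive a repair can be, so confounding by indication is to be expected.

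**Working it through.** The plan gives no figure for the performance of the screen, so there is nothing to reproduce. The checks below show how the rule behaves under stated assumptions.

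**1. Chance that a prognostic covariate passes the screen, full cohort**

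Inputs from the protocol: about 6000 patients (the expected registry size) and a 5% outcome (the complement of the 95% freedom from distal reoperation assumed in the Sample size calculation). Assumed: a binary covariate with 10% prevalence and odds ratio 1.5.

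- Group risks solve 0.10·p1 + 0.90·p0 = 0.05 with odds(p1) = 1.5·odds(p0). This gives p1 = 0.0700 and p0 = 0.0478, a difference of 0.0222.
- SE = √(0.0700·0.9300/600 + 0.0478·0.9522/5400) = 0.0108, so z is about 2.05.
- P(pass at 0.05) = Φ(2.05 − 1.96), about 54%: **lost in about 46%**.
- P(pass at 0.2) = Φ(2.05 − 1.28), about 78%: **lost in about 22%**.

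A pooled standard error, √(0.05·0.95·(1/600 + 1/5400)) = 0.0094, gives z of about 2.37 and losses of about 34% and 14%. The pattern is the same.

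For contrast, take a 17% outcome (the 30-day mortality level cited in the Background) with the same covariate. The risks are 22.7% and 16.4%, the SE is 0.0178 and z is about 3.55. The losses fall to about 6% and 1%. The screen is weakest where the outcome is sparse.

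**2. The same question on the hazard scale**

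P(pass) = Φ(√(d·π·(1 − π))·ln HR − z for the cut-off), where d is the number of events and π the prevalence. With d = 200, π = 0.10 and HR 1.3: √(200·0.09)·0.262 = 1.11. The covariate passes in about 20% at p < 0.05 and 43% at p < 0.2. Over assumed ranges of 100 to 300 events, 5 to 20% prevalence and HR 1.3 to 1.5, the pass rate runs from 8% to 80% at p < 0.05 and from 24% to 94% at p < 0.2.

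**3. Effect on a regression-adjusted treatment estimate**

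This was a Cox simulation with 4000 patients, a 5% baseline probability of treatment (the protocol says "We assume that about 5% of patients have undergone total arch repair in this collaborative registry") and a true treatment HR of 1.00. It assumed eight binary confounders, each with 15% prevalence, OR 1.8 with treatment and HR 1.25 with the outcome. There were 200 replicates.

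| Adjustment | Confounders kept | Mean HR | Rejection at 0.05 |
|---|---|---|---|
| All eight, pre-specified | 100% | 1.006 | 5.5% |
| Screen at p < 0.05 | 28% | 1.075 | 9.5% |
| Screen at p < 0.2 | 53% | 1.033 | 7.5% |
| Whichever screen gives the smaller treatment p-value | – | 1.059 | 9.5% |

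The Monte Carlo SE of the rejection rates is about 1.6 to 2.1 percentage points. The differences in rejection are therefore imprecise; the ordering of the mean HRs follows the share of confounders kept.

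**The case against.** The strongest reply is that the main treatment comparisons are already protected. The propensity model is non-parsimonious, unscreened and clustered by centre, and matched cohorts are checked against a standardized difference of 0.10. This stands. A reader might infer that the univariate rule biases every comparison of surgical strategies, but the weighted and matched analyses do not use it. For the same reason, a low pass rate computed inside a matched set of 200 pairs would say little about confounding, because matching is meant to have balanced the covariate already.

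The reply does not remove the fault. The rule covers regression models without exception, nothing ranks the propensity analysis above a screened Cox or subdistribution estimate, and the propensity score does not serve the aim of identifying risk factors.

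Three further readings are tempting but unsupported:

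- **That the cut-off is chosen after seeing results.** The text does not say when the choice is made, and covariates of interest can be counted beforehand. What it does show is that no trigger is fixed.
- **That year of surgery is left out.** It is not among the variables defined in the article, but an article condenses its list, and nothing excludes it from the baseline variables.
- **That the risk score shares the fault.** It does have a univariate step ("Univariate analysis will be performed on all candidate covariates of the derivation dataset to identify predictors of in-hospital mortality"), but its aim is prediction. Its variables come from stepwise selection over bootstrap samples followed by the Akaike criterion, and it is tested in a held-out quarter of the data.

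It is also fair to say that the simulated bias is modest, and that it depends on eight confounders all acting in one direction.

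**Conclusion.** The point holds for the regression-adjusted treatment effects and risk-factor models fitted by Cox or subdistribution-hazard regression. As written, the rule can omit real confounders, permits two different models on the same data, and yields confidence intervals that ignore the selection. It is a stated method, not a detail left for a later document.

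On the illustrative inputs, a prognostic covariate is lost in about 46% of analyses at p < 0.05 and about 22% at p < 0.2. The odds ratio and prevalence are assumptions. That calculation concerns loss of a prognostic factor; it does not measure bias, because it assumes no link to treatment. The simulation does include such a link. It suggests a shift in a null HR to between 1.03 and 1.08, with false rejection of 7.5 to 9.5% against 5.5% under full adjustment, within the simulation error given above. The change should be made, but the point does not undermine the propensity-based comparisons.

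**What to change.** Delete the univariate entry rule. For the Cox and subdistribution-hazard models, name an adjustment set in advance on clinical grounds and size it to the expected number of events. Candidates are age, sex, urgency class, malperfusion, renal function, genetic syndrome, extent of dissection, year of surgery and centre. Where events are too few to carry the set, as may happen for reoperation, adjust through the propensity score already planned or use penalised estimation.

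The cost is a change of wording. The candidate covariates are either collected already or follow from routine data such as the date of surgery. The small downside is somewhat wider confidence intervals from keeping weak covariates.

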Interinstitutional and between-surgeons differences in terms of early outcomes will be evaluated using mixed-effects logistic regression. The risk-adjusted rate of adverse binary events at each center will estimated by dividing the observed number of adverse events by the expected number of adverse events, and by multiplying this ratio by the average event rate of the overall series. The expected numbers of adverse events will be calculated with logistic regression. The estimated risk-adjusted rates of adverse events will be summarized as odds ratios and their 95% confidence intervals in caterpillar plots with the x-axis ordered for increasing adjusted rates.

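### One random 75/25 split for the mortality score is valid but wasteful, and cannot show how the score performs in a centre not used to build it

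*Protocol article*

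**What the plan says.** The Statistical analysis section of the protocol article sets out how the risk score will be made. For this purpose "the study cohort will be randomly divided into two datasets", in proportions of 75.0% and 25.0%.

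- **Screening:** "Univariate analysis will be performed on all candidate covariates of the derivation dataset to identify predictors of in-hospital mortality". Multiple logistic regression is then run in the same derivation data.
- **Resampling:** "A stepwise procedure with a bootstrap approach will be used, and 100 samples will be extracted with a size of 70% of the derivation dataset". Variables chosen in at least half of these samples enter the model, followed by forward selection on the Akaike criterion. Resampling therefore serves variable selection, not the estimation of optimism.
- **Validation:** "The model will be tested in the validation data set for calibration, using the Hosmer–Lemeshow test, and for discrimination using the receiver-operating characteristic curve analysis".
- **Comparison with existing scores:** this "will be performed in the overall dataset as well as in the validation dataset using the DeLong test".

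The section describes no refit on all patients, no repeated split, and no hold-out by centre, country or period. Centre enters elsewhere: "Interinstitutional and between-surgeons differences in terms of early outcomes will be evaluated using mixed-effects logistic regression". The propensity model is also multilevel because results may vary with each centre's referral and care. The Limitations section adds that care may differ between institutions and surgeons and that these effects belong in every analysis.

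**The concern.** Two things are at stake.

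The first is efficiency. A single split withholds a quarter of the deaths from model building and then measures performance on that quarter alone. Resampling the full model-building procedure uses every patient for both purposes and does not hang the published performance on one random draw.

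The second is what the validation can answer. A patient-level random split gives two parts that differ only by chance. Good performance in the second part shows that the model was not badly overfitted. It says nothing about a hospital that contributed no patients to the derivation data. With 19 centres, and an explicit expectation that centres differ, the registry could address that question, and the stated design does not.

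**Working it through.** **Inputs from the protocol article**
- Registry size: "The participating hospitals are expected to provide a sample size of more than 6000 patients" (Sample size calculation). Check: 19 centres × 20 procedures a year × 16.25 years (January 2005 to March 2021) = 6175, consistent with that figure. I use 6000.
- Early mortality: cited 30-day rates of 16.9%, 17% and 18% (Background). I use 17% as a proxy for in-hospital death.
- Split 75/25; 19 centres.

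**Assumptions (not in the article):** AUC between 0.70 and 0.80; correlation of 0.5 to 0.7 between two scores' AUC estimates.

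**Deaths**
- Total: 6000 × 0.17 = 1020.
- Derivation: 0.75 × 1020 = 765. Validation: 0.25 × 1020 = 255, among 1500 patients (1245 survivors).
- Across 16.9% to 18% mortality: 1014 to 1080 in total, 254 to 270 in validation.

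**Precision of the AUC (Hanley–McNeil)**

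Var = [A(1−A) + (n₁−1)(q₁−A²) + (n₀−1)(q₂−A²)] / (n₁n₀), with q₁ = A/(2−A) and q₂ = 2A²/(1+A). For A = 0.75: q₁ = 0.600, q₂ = 0.643, A² = 0.5625.
- Validation part (255 deaths, 1245 survivors): SE = 0.0186; half-width 1.96 × 0.0186 = 0.036.
- All patients (1020 and 4980): SE = 0.0093; half-width 0.018.
- At A = 0.70 and 0.80 the validation half-widths are 0.038 and 0.034.
- Split-to-split SD of the AUC for a fixed model: 0.0186 × √0.75 = 0.016.

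**Calibration in the validation part**
- Observed/expected ratio: SE of the log = √[(1−0.17)/255] = 0.057, an interval factor of 0.89 to 1.12. With 1020 deaths it is 0.95 to 1.06.
- Calibration slope, from the logistic information with a normal linear predictor giving AUC 0.75: ±0.17, against ±0.085 in all patients.

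The all-patient figures are sampling error only. They leave out the uncertainty of an optimism correction, so the twofold contrast is a best case for the alternative.

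**Comparison with existing scores**
- Smallest AUC difference detectable in the validation part with 80% power: 2.80 × SE × √[2(1−r)]. For r = 0.5 this is 2.80 × 0.0186 × 1.00 = 0.052; for r = 0.7 it is 2.80 × 0.0186 × 0.775 = 0.040.
- In the overall dataset, three quarters of the patients are those on whom the new score was fitted, so that comparison leans towards the new score.

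**Centres**
- Average centre: 6000/19 = 316 patients and 316 × 0.17 = 54 deaths.
- Chance that such a centre is absent from the validation part: 0.75³¹⁶, effectively nil. Even for a centre with 50 patients it is 0.75⁵⁰, about 6 in 10 million. Both parts therefore hold the same centres.

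**Range in registry size (AUC 0.75).** With 4000 patients, 169 to 180 validation deaths and a half-width of about 0.044. With 7719 (25 a year per centre, the volume in the Discussion), 326 to 347 deaths and about 0.032.

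**The case against.** The strongest defence is that nothing here is in error. The split is fully described, the held-out quarter is untouched by selection, and its performance estimate is valid. That stands. So does the point about absolute size: 255 deaths and ±0.036 is moderate precision.

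The loss to the model itself is also probably small. A simulation with 30 candidate predictors (12 real), 17% mortality and AUC near 0.75 gave a mean out-of-sample AUC of 0.740 when fitted on 4500 patients and 0.742 on 6000. It fitted all predictors without stepwise selection, so it is only indicative.

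Three stronger readings are tempting, and the article does not support them.
- A reader might infer that selection rests on only 70% of the derivation data. It does not: 100 such samples are drawn, which together cover the derivation patients, and the regression is run in the derivation dataset.
- A reader might infer that the plan presents the score as transportable. It does not: the 25% is called a validation set, never an external one.
- A reader might take the analysis of differences between institutions as contradicting the split. It is a separate analysis of outcomes, which neither validates the score by centre nor conflicts with the split.

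It can also be said that the validation scheme belongs in a statistical analysis plan. The article, however, does not leave it open; it names a specific scheme, and that choice can be judged.

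**Conclusion.** The point holds as one of efficiency and scope, not of bias. The stated split keeps about 255 of 1020 expected deaths out of the model and reports an AUC from one draw with a half-width of about 0.036, roughly twice the 0.018 that sampling error alone would give in all patients. The split cannot test the score in a centre not used to build it, although the article says centre effects should be considered throughout. Of the two planned comparisons with existing scores, only the one in the validation part is free of derivation patients, and it can detect AUC differences of only about 0.04 to 0.05.

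These sizes assume 6000 patients, 30-day mortality as a proxy for in-hospital death, an AUC near 0.75 and, for the comparison, a correlation of 0.5 to 0.7. That a quarter of the deaths is withheld and that the same centres sit in both parts depend on none of these values. The registry's primary outcomes and the arch-repair comparison are unaffected. The change is worth making but is not essential to the registry's validity.

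**What to change.** Replace the single split with the following.

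1. Build the score on all patients.
2. Estimate optimism in AUC and calibration by bootstrapping the whole procedure: univariate screening, the repeated stepwise selection, the Akaike step and the final fit.
3. Add internal-external cross-validation, leaving out one centre at a time, or one country or group of centres where deaths are few. Report pooled AUC, calibration slope and intercept.
4. Base the comparison with existing scores on the optimism-corrected or held-out predictions, not on the overall dataset as now described.

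Data collection does not change. The costs are more computing, since the selection procedure is itself repeated within each bootstrap replicate; noisy results for single centres (about 54 deaths in an average one), which is why pooled measures should lead; and no single validation cohort to display.

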## Background

Acute Stanford type A aortic dissection (TAAD) is a life-threatening condition. Surgery is usually performed as a salvage procedure and is associated with increased postoperative early mortality and morbidity [1]. Although early mortality has declined during the last years [2], the recent The Nordic Consortium for Acute Type A Aortic Dissection registry including 1189 patients operated from 2005 to 2015 in 8 centers showed that 30-day mortality after surgery for acute TAAD was as high as 18% [3]. The multicentre, prospective German Registry for Acute Aortic Dissection type A including 2137 TAAD patients operated from 2006 and 2010 documented a 30-day mortality of 16.9% [4]. A more recent analysis of the Society of Thoracic Surgeon database including 7353 patients operated from 2014 and 2017 for acute TAAD reported a 30-day mortality of 17% [5]. Furthermore, surgery for TAAD is often complicated by major adverse events such as stroke [5] and acute kidney failure [6], which may have a significant impact on late survival. In this scenario of significant postoperative mortality and morbidity, surgeon faces the controversial issue of the extent of surgical repair for acute TAAD by avoiding a major surgical repair, which may increase the risk of early adverse events, and by resecting segments of the aorta which otherwise may expose the patient to the risk of late aortic-related complications [7, 8]. Understanding the balance between the patient’s conditions which may not allow extensive procedure and those treatment strategies which may limit the risk of late adverse events in patients who remain alive long after the surgery is essential for an appropriate management of TAAD. However, previous registries [1, 3] did not provide information on the long-term durability of these procedures. We have planned the multicenter European registry of surgery for acute TAAD (ERTAAD) to evaluate the contemporary early outcomes and the durability of different surgical strategies for acute TAAD at 15 years in a large study population.

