## Discussion

### Implications for the treatment of TAAD patients

Analysis of the data from this collaborative registry will allow analysis of contemporary results of a large number of TAAD patients with a rather long follow-up period. We expect that the multicentre nature of this registry will allow reduction in the risk of bias related to institutional volume and surgical experience. In fact, all the participating centers have an annually rate of at least 25 procedures for acute TAAD and have an aortic surgery program which would facilitate an adequate follow-up and management of possible late aortic events after primary repair of TAAD. Therefore, we expect to gather data which will provide important insights into the assessment of the operative risk of patients with acute TAAD and conclusive results on the value of different surgical and perfusion strategies for this emergency condition.

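### The in-hospital mortality score is built by three rounds of data-driven selection with no stated shrinkage, so its predicted risks are expected to be mildly to moderately too extreme in new patients

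*Protocol article*

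**What the plan says.** The protocol article, under Statistical analysis, sets out the score's development as a sequence:

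1. A random split into "the derivation data set (75.0% of patients) and the validation data set (25.0% of patients").
2. A univariate screen of all candidates in the derivation set.
3. Stepwise logistic regression in 100 samples, each 70% of the derivation set, with limits of 0.05 to stay and 0.1 to enter. "Variables selected in at least 50% of the stepwise procedures will be included in the regression model".
4. Forward addition of further covariates by AIC, "until the inclusion of a new covariate determined an increase in the Akaike information criterion value".
5. Testing in the validation set: the Hosmer-Lemeshow test for calibration and the ROC curve for discrimination.
6. Comparison with existing scores by the DeLong test, the net reclassification index and the integrated discrimination improvement, then Kaplan-Meier curves by score decile.

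No shrinkage, penalisation or recalibration is stated between steps 4 and 5. The section gives no number of candidates and no expected AUC. Under Implications for the treatment of TAAD patients, the registry is expected to give "important insights into the assessment of the operative risk of patients with acute TAAD", so absolute risks matter.

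**The concern.** Coefficients that survive selection in the same data tend to be too far from zero. If they go into the score unadjusted, the spread of predicted risk in new patients is too wide and the calibration slope falls below 1. Resampling could be used to estimate and remove this excess, but here it only decides which variables enter.

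What is at stake is the absolute risk attached to a patient, above all at the high end. The integrated discrimination improvement compares mean predicted risks, so over-dispersed predictions can flatter the new score on that measure. The net reclassification index can be affected in part.

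**Working it through.** **Inputs from the protocol article**

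- Sample size calculation: "The participating hospitals are expected to provide a sample size of more than 6000 patients". Check: 19 centres × 16.25 years × 20 procedures per year = 6175, which agrees.
- Same section: "a study population of 4000 patients would be enough". This was set for the arch-repair question and serves here only as a lower case.
- The 75/25 split gives 4500 and 1500 patients at 6000, and 3000 and 1000 at 4000.
- Background: one cited database "reported a 30-day mortality of 17" per cent; in one cited registry "30-day mortality after surgery for acute TAAD was as high as 18" per cent. Taking 17% 30-day mortality as a proxy for in-hospital mortality gives 0.17 × 4500 = 765 derivation deaths, or 0.17 × 3000 = 510.

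**Assumptions not in the documents**

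40 to 100 candidate parameters, 12 to 15 of them true predictors; AUC 0.70 to 0.75; correlation between predictors 0 or 0.1.

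**Step 1: heuristic for a model with all candidates**

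Expected slope = LR / (LR + P), where LR is the model's likelihood-ratio chi-square implied by the AUC and 17% mortality, and P is the number of parameters.

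| Registry | AUC | LR | P = 40 | P = 60 | P = 100 |
|---|---|---|---|---|---|
| 6000 | 0.70 | about 336 | 0.89 | 0.85 | 0.77 |
| 6000 | 0.75 | about 538 | 0.93 | 0.90 | 0.84 |
| 4000 | 0.70 | about 224 | 0.85 | 0.79 | 0.69 |
| 4000 | 0.75 | about 359 | 0.90 | 0.86 | 0.78 |

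Example: 538 / (538 + 60) = 0.90. These are pessimistic for the planned procedure, because the 50% rule discards many noise variables.

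**Step 2: simulation of the described sequence**

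Univariate screen at p < 0.05; stepwise in 70% resamples, approximated by backward elimination at p < 0.05; the 50% rule; forward AIC; ordinary logistic fit. The slope was measured against true risks in 100,000 new patients. The text leaves open whether forward AIC searches all candidates or only the screened ones, so both were run. Mean slopes:

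| Registry | AIC over all: 40 candidates | 60 | 100 | AIC over screened only, 40 to 100 |
|---|---|---|---|---|
| 6000 | 0.92–0.95 | 0.87–0.94 | 0.86–0.89 | 0.89–0.97 |
| 4000 | 0.88–0.93 | 0.85–0.90 | 0.80–0.86 | 0.89–0.95 |

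The runs were small (8 to 16 replicates per scenario, 12 to 100 resamples; standard error about 0.01 to 0.02). Where the spread was examined, single-dataset slopes ran from 0.78 to 0.99 at 6000 and from 0.76 to 1.01 at 4000. A further short run with the screen at p < 0.2, 4500 derivation patients, about 16% mortality and 40 to 60 candidates gave mean slopes of 0.88 to 0.94.

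**Step 3: size on the risk scale**

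In simulations with 60 candidates, about 16% mortality and no univariate screen, predicted against observed mortality in the top risk decile was 46% against 44% at slope 0.93, 43% against 40% at 0.89, and 39% against 34% at 0.81.

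**Step 4: would the planned test notice?**

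Simulated power of the Hosmer-Lemeshow test (ten groups, 5% level), over AUC of about 0.70 to 0.75:

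| True slope | 1500 validation patients | 1000 |
|---|---|---|
| 0.90 | 12–14% | 9–13% |
| 0.85 | 20–28% | 16–22% |
| 0.80 | 39–52% | 27–40% |

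**Step 5: which results move?**

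Multiplying the linear predictor by one positive factor and resetting the intercept preserves the ranking of patients. AUC, the DeLong test and the decile groups therefore stay the same. Predicted risks and the integrated discrimination improvement change, and partly the net reclassification index.

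**The case against.** **The text is silent on the final coefficients.** It does not say how they are estimated or turned into points, and this is a condensed article whose full protocol and analysis plan are not shown. A reader might infer that the plan rules shrinkage out; it does not. What remains is that the sequence is given down to its p-value limits and passes directly from selection to testing. Followed as printed, it yields ordinary logistic coefficients, and a shrinkage step would have to be added to it.

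**The overfitting may be mild.** With about 765 deaths and 40 candidates at 6000 patients, the mean slope is 0.92 to 0.97. A slope near 0.80 appeared only with 100 candidates, 4000 patients and AUC about 0.70. A validation decile holds about 150 patients, where a 40% rate has a standard error of √(0.4 × 0.6 / 150) = 4 points, so a gap of 2 to 3 points is within noise there. This stands and limits the size of the point.

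**A quarter of patients is held out.** Performance measured there is not inflated by selection. That is true, but holding data out reveals miscalibration without correcting it, and the test named would usually miss it.

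**The comparison with existing scores.** A reader might infer that all of it is distorted. It is not: the rank-based parts are unaffected by uniform shrinkage.

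**Conclusion.** The point holds as an expected, mild to moderate overfitting of absolute risk. Under the stated assumptions the mean calibration slope is about 0.86 to 0.97 at the expected 6000 patients and about 0.80 to 0.95 at 4000. It was below 1 in every scenario simulated, but a single dataset can come close to 1, so it is not certain that this score will be too extreme. The size rests on an assumed candidate count and AUC and on 30-day mortality as a proxy, so it cannot be read from the documents as one figure. They do not support a claim that the score will be badly miscalibrated or that its discrimination is overstated for lack of shrinkage. The change is worth making because it is cheap and nothing in the stated sequence does the same job.

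**What to change.** Add to the risk-score paragraph: after selection, a uniform shrinkage factor will be estimated by repeating the whole selection (univariate screen, stepwise with the 50% rule, forward AIC) in bootstrap samples of the derivation set. The coefficients will be multiplied by this factor and the intercept re-estimated before the score is formed. The alternative is to fit the candidates by penalised (ridge or lasso) logistic regression. Use the resulting model in every validation and comparison step.

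In the short run with the p < 0.2 screen, the whole-procedure bootstrap factor moved the mean slope from 0.88–0.94 to 0.98–1.08. The simpler factor 1 − candidates / LR of the full model, tried without the univariate screen, gave 0.98–1.06. The penalised alternative was not simulated here.

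The cost is a sentence or two and some computing time. Predicted risks will look slightly less extreme, and slight over-shrinkage is possible, as the upper ends of these ranges show. If the overfitting proves mild, the factor should be near 1 and little changes.
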